### Usual care

At both recruitment centres, usual physiotherapy after discharge following TKR surgery comprises information and advice on knee-specific and functional exercise. Referral for outpatient physiotherapy is on a needs-only basis when deemed appropriate by a member of the clinical care team. Prior to hospital discharge, patients are assessed on an individual basis by the inpatient physiotherapy team at each centre, and patients with poor range of motion or muscular weakness are referred for outpatient community-based physiotherapy. This referral is at the discretion of the hospital’s physiotherapy or orthopaedic team. General practitioners (GPs) and consultants can also refer patients for outpatient physiotherapy as appropriate. Use of physiotherapy services by participants in both trial arms will be recorded in the trial questionnaires.

### Intervention

Participants allocated to the intervention group will receive the intervention in addition to usual care. The intervention is a novel weekly 1-hour physiotherapy class, starting 6 weeks after surgery and then on a weekly basis over 6 consecutive weeks. Previous trials have evaluated outpatient physiotherapy after TKR [20]; however, this intervention is novel as it embeds individualised exercises within a group-based task-oriented exercise circuit. The design of the intervention was informed by intervention development work, which included a systematic review [20], survey of current practice [14] and a feasibility study to pilot the intervention [25]. The intervention consists of task-orientated exercises and individualised exercises. Previous research has demonstrated the benefits of task-orientated, functional exercises [19] and the importance of improving patients’ ability to participate in ‘valued activities’ [8, 29]. Task-orientated exercises have been found to be more effective than traditional exercises, such as range of motion exercises, in improving function and participation after TKR [19] and other conditions such as stroke [30]. The inclusion of individualised exercises aims to address patients’ expectations, empower people to take an active role in rehabilitation, and increase self-efficacy [31, 32]. Delivery is in a group-based setting, which can be a cost-effective way to deliver rehabilitation without compromising effectiveness [33–35]. There is currently no consensus on the optimal treatment frequency or number of sessions for physiotherapy after TKR [36]. The intensity of our intervention was informed by previous research [20], combined with the need to develop an intervention that would be deliverable within the NHS if proven to be effective.

Classes will be held at set weekly times in an outpatient gymnasium at a large NHS hospital and up to a maximum of 12 patients can attend a class. Classes will be supervised by a physiotherapist and physiotherapy technician/assistant, and will run on a rolling system so that new patients can join the classes each week as other patients finish the class. Participants will be reimbursed travel costs that are incurred for their travel to attend classes. Before attending the physiotherapy classes, participants will be asked to complete an Activity Goal Form which involves identifying two functional goals that they would like to achieve. In their first class, each participant will have a discussion with the physiotherapist about these goals to develop two individualised exercises which they begin in their second class. Participants will also be given an exercise booklet in which they record details about their weekly progress in the class.

Each class will involve a short warm up, after which patients follow a simple exercise circuit. The 5-min warm up involves participants mobilising around the gym circuit at a steady pace. This is interspersed with gentle upper limb and lower limb movements including shoulder circumduction, elbow flexion and extension, hip and knee flexion, and ankle circumduction exercises, as each participant is able. The exercise circuit involves 12 exercise stations, including two stations dedicated to individualised exercises. An overview of the exercises stations is provided in Table 1. Four minutes is allocated to each station to provide patients with sufficient time to carry out the exercises at their own pace. The exercises are designed to increase lower limb strength, balance, function and confidence using specific and task-related activities. A selection of graded exercises is provided at each station to enable the patients to exercise at a level suitable to their ability. During weeks 2–6, the exercises are progressed on an individual basis through discussion with the physiotherapists.

**Table 1 Tab1:** Brief description of exercises at each station within the physiotherapy class

Station and exercise	Description	Task
1. Bed-based exercises	Low-grade exercises including knee flexion and extension range of motion (2 × 8 repetitions), quadriceps strengthening (2 × 8 repetitions), hamstring strengthening (2 × 8 repetitions), quadriceps stretching (2 × 5 repetitions), and hamstring stretching (2 × 5 repetitions). Progressions include increasing number of repetitions, changing position, and addition of resistance bands or ankle weights	Maintain/improve knee range of motion and strength, simulation of kicking/swimming
2. Getting in/out of bed	Practice turning from back to side and to sitting. Then stand from sitting. Return to sitting then lying (2 × 5 repetitions). Progression includes bridging then sit to stand	Practice transferring in and out of bed log rolling, and sit to stand
3. Balance tasks	Balanced-based exercises including single leg stance (3 × 30 sec) and wobble board (3 × 30 sec). Progressions including increasing duration and including upper limb actions such as throwing, catching and reaching	Improve static and dynamic balance. Falls prevention
4. Stair exercises	Stepping up and down on stairs of varying height (3 × 8 step-ups). Progression includes using higher step	Stair ascent and descent
5. Individualised exercise 1	Exercise designed specifically for individual patients	Individual task
6. Walking exercises	Walking practice (gait re-education). Progressions including from aided to unaided, side stepping, walking over uneven surfaces, walking carrying objects	Walking. Falls prevention
7. Squatting and crouching	Mini and semi-squats (3 × 8 repetitions). Squats can be performed with the assistance of chairs and gym ball. Progressions including increasing the depth of squat and crouching	Squatting and crouching down
8. Cycling	Static bike (1 min cycling followed by 30 sec rest and then repeat). Progressions include increasing resistance and duration of cycling	Improve cardiovascular fitness and knee range of motion
9. Gardening/kneeling	Replicating digging action using stepper (3 × 8 repetitions) with progression including increasing resistance of stepper. Kneeling onto cushioned or hard surfaces (3 × 8 repetitions) with progression including full kneeling and high kneeling. Activities to desensitise the knee joint such as light pressure using different textures (30–60 sec)	Improve kneeling ability
10. Lunges	Mini lunges (2 × 8 repetitions). Progressions include depth of lunge, lunge walking and lunge to bowling or picking up objects	Improve knee strength and ability to picking objects up from floor
11. Individualised exercise 2	Exercise designed specifically for individual patients	Individual task
12. Treadmill/cross-trainer	Practice straight-line walking. Progressions including increase in speed and incline of treadmill, use of cross-trainer	Walking on flat and uphill. Jogging
		Improve cardiovascular fitness

Towards the end of the intervention, the physiotherapist will spend time with each participant to develop their home exercise programme. Every participant will be provided with an individualised written plan detailing the key exercises to continue at home. Advice on number of repetitions and how often the exercises should be performed will be provided, tailored to the participant’s individual ability.

### Assessment times

Participants will be followed up for 12 months after TKR. Participants will be asked to complete questionnaires before their surgery and at 3 months, 6 months and 12 months after their surgery. Post-operative questionnaires will be posted to participants, followed by a postal reminder and a telephone call to non-responders.

In addition to the questionnaires, further information will be collected by telephone. At 2 weeks post-operative, all participants will be telephoned and asked to complete the five-level EuroQol questionnaire (EQ-5D-5 L) [37]. Patients who attend the intervention will be telephoned 1 month after completion of the classes to complete a short telephone survey to evaluate the classes and home exercise programme. All participants who complete the 12-month follow-up of the trial will be contacted by telephone and asked if they would be willing to complete a telephone survey about the experience of trial participation. A flow chart of trial participation is provided in Fig. 1.

**Fig. 1 Fig1:**
[figure not shown]
Flow chart of trial participation

### Primary outcome

The primary outcome is the Lower Extremity Functional Scale (LEFS) [26] at 12 months post-operative. The LEFS is a validated 20-item questionnaire which assesses lower limb function and difficulty in performing everyday tasks. The LEFS has been recommended as the outcome measure of choice to measure function in patients with knee OA and those undergoing joint replacement because of its good psychometric properties and minimal floor and ceiling effects [38–40].

### Secondary outcomes

Secondary outcomes include quality of life, knee pain, knee function, depression, anxiety and patient satisfaction. These outcomes will be assessed using the following validated measures at 3, 6 and 12 months post-operative, except where indicated:EQ-5D-5L [37]: measures quality of life and allows derivation of incremental quality adjusted-life years (QALYs) for the economic evaluation. In addition to the standard assessment time points, the EQ-5D-5L will be administered by telephone at 2 weeks after surgeryLEFS at 3 months and 6 months post-operativeKnee Injury and Osteoarthritis Outcome Score (KOOS) [41]: assesses pain, other symptoms, function in daily living, function in sport and recreation and knee-related quality of lifeHospital Anxiety and Depression Scale (HADS) [42]: assesses symptoms of depression and anxietySelf-Administered Patient Satisfaction Scale for Primary Hip and Knee Arthroplasty [43]: assesses satisfaction with the outcome of knee replacementLikert-type scale for satisfaction with physiotherapy treatment received

### Resource use

Resource-use data will be collected from hospital discharge to 12 months post-operative. Resources required to deliver the intervention will be recorded in Case Report Forms by the physiotherapists delivering the intervention. Patient self-report use of services will be collected through patient-completed resource-use questionnaires. The questions will cover the use of additional physiotherapy treatments in hospital and community and other therapies prescribed, readmissions, outpatient visits, GP and nurse visits, medication use and use of social services. To allow for a secondary societal analysis, questionnaires will further collect time off work, leisure activities, private expenditures (e.g. privately paid therapies, travel costs to sessions) and informal care. All participants will be provided with a resource-use log to prospectively fill in resources used to aid them in the completion of the resource-use questionnaires [44].

### Patient characteristics

Data on socioeconomic status (marital status, living arrangements, ethnicity, educational attainment, working status), medical co-morbidities (Functional Co-morbidity Index [45]), knee symptoms (LEFS, KOOS), quality of life (EQ-5D-5L), and depression and anxiety (HADS) will be collected in the pre-operative questionnaire to allow adjustment for these variables in the analysis. Data on age and gender will be collected by the researcher at recruitment.

### Patient satisfaction, adherence and perceived value of the physiotherapy classes

Patients who are randomised to the intervention group and attend the physiotherapy classes will be telephoned by a member of the research team 1 month after completion of the classes and asked if they would be willing to answer questions about the physiotherapy classes and home exercise programme. Participants will be asked questions about satisfaction with the classes, ability to achieve personal goals and aspects of the class that they found helpful or unhelpful. To evaluate the home exercise programme, participants will be asked about how often they have been performing their home exercises, any barriers or facilitators to performing the exercises, and any perceived value/benefits of performing the exercises. Responses to the questions will be recorded by a researcher on a standardised proforma.

### Trial evaluation

Brief structured telephone interviews to evaluate trial participation will be conducted with participants after completion of the 12-month post-operative questionnaire. Interview questions will be open-ended and will cover reasons for participating in the trial, experiences of trial participation, and any perceived benefits or negative aspects to participating in the trial. Participants’ responses will be recorded by a member of the research team on a standardised proforma. In addition, patients who self-withdraw from the trial will be asked if they would be willing to discuss their reasons for withdrawal with a member of the research team.

### Adverse events

Data on adverse events and serious adverse events will be collected and closely monitored to ensure the ongoing safety of participants. Adverse events will be recorded on a standardised Adverse Events Report Form. All serious adverse events will be notified to the study sponsor and reviewed by the Trial Steering Committee.

### Sample size

The minimal clinically important difference (MCID) for the LEFS is 9 scale points [26]. In our feasibility study, we observed a pooled standard deviation (SD) of 18.4 and a rate of missing LEFS score of 9 % in the intervention group and 35 % in the usual-care group at 6 months post-operative. For the purposes of the sample size calculation we assumed a similar SD for the LEFS at 12 months post-operative, due to the lack of relevant published data. To account for the uncertainty induced by estimating parameters from a small feasibility study, we adjusted the assessed sample by an inflation factor of 1.12^2^, a value derived from the 80 % upper confidence limit of the SD estimate [46]. We also accounted for a missing data rate of 35 %, although we are implementing additional measures to improve LEFS completion rates (e.g. completion of the primary outcome measure over the telephone with non-responders). Therefore, a sample of 256 patients will allow us to detect a MCID (9 points) in the LEFS between trial arms at 12 months post-operative, assuming a power of 80 %, a two-sided 5 % significance level and accounting for up to 35 % missing data and an ‘inflation factor’ of 1.12^2^.

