## Methods/design

The ARENA study (Activity-orientated REhabilitation following kNee Arthroplasty) is a multi-centre, pragmatic, superiority RCT to evaluate the long-term effectiveness and cost-effectiveness of outpatient group-based physiotherapy after TKR in addition to usual care. The trial has been approved by the National Research Ethics Committee South West – Central Bristol (reference 14/SW/1144) and is registered on the ISRCTN registry (ISRCTN32087234). The trial is informed by a feasibility study of the RCT with 46 patients and a 6-month post-operative follow-up [25]. In this study, the intervention was developed and the feasibility of delivering the intervention to patients with TKR in the context of a RCT was evaluated. The trial was developed in collaboration with the Patient Experience Partnership in Research (PEP-R) group [26], a dedicated, specialised patient-involvement group comprising 16 patients with musculoskeletal conditions, many of whom have had joint replacement.

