### Randomisation

Participants will be randomised with a 1:1 treatment allocation to the intervention group or usual care group 2 weeks after TKR. Prior to randomisation, eligibility criteria will be reassessed through contact with participants and review of operation notes. Randomisation with allocation concealment will be conducted by means of a computer-generated code, administered centrally and communicated via the Internet (through the Bristol Clinical Trials and Evaluation Unit). Randomisation will be stratified by pre-operative function measured by the Lower Extremity Functional Scale [27] (categorised as high or low function based on mean scores from a published study with a similar patient cohort [28]) and recruitment centre (Southmead Hospital or Emersons Green Treatment Centre). Blinding of participants and trial personnel to treatment allocation will not be possible due to the nature of the intervention.

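### The protocol rules out blinding for all trial personnel, but its reason does not reach staff who complete the primary LEFS by telephone, and such calls may fall mostly in usual care

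*Protocol article*

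**What the plan says.** All statements are in the Protocol article.

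- Assessment times: "Post-operative questionnaires will be posted to participants, followed by a postal reminder and a telephone call to non-responders".
- Sample size: the steps to improve LEFS completion include, as an example, "completion of the primary outcome measure over the telephone with non-responders".
- Randomisation: "Blinding of participants and trial personnel to treatment allocation will not be possible due to the nature of the intervention".
- Sample size: the feasibility study had a "rate of missing LEFS score of 9 % in the intervention group and 35 % in the usual-care group at 6 months post-operative". Methods/design describes it as a "feasibility study of the RCT with 46 patients and a 6-month post-operative follow-up".
- Section on satisfaction, adherence and perceived value of the classes: someone from the research team telephones class attenders one month after the classes end. Only intervention participants receive this call.
- Discussion: lack of blinding is listed as a limitation, explained by the group format, and the bias named is that of participants who report their own outcomes and know their arm. Telephone follow-up appears only as a strength for completion rates.

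**The concern.** The Randomisation sentence treats every role alike. A participant in a weekly class cannot be blinded to it, nor can the physiotherapist who runs it. A person who reads out 20 LEFS items months later can be, since the task needs no knowledge of the arm. As written, the protocol gives up a safeguard that is available for part of its primary outcome data.

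This matters more if telephone completion is unevenly spread. A shift between telephone and postal scores, or the influence of an interviewer who knows the arm, cancels only when the telephone share is the same in both arms. Otherwise it passes into the 12-month LEFS difference. Multiple imputation does not address it, because a score taken by telephone counts as observed. An analysis plan cannot mask a caller afterwards.

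The class-survey calls add a practical route to unmasking. Classes start 6 weeks after surgery and run weekly for 6 weeks, so a call one month later falls at about 4 months, before the 6- and 12-month questionnaires. The article does not separate that caller from the LEFS caller.

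**Working it through.** **Inputs from the Protocol article.** 128 per arm; MCID 9; SD 18.4; inflation factor 1.12² on the sample size; 80% power; two-sided 5%; missing-data allowance 35%; feasibility missing LEFS 9% and 35%; feasibility study of 46 patients.

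**Assumptions, not in the documents.** A telephone shift m of 2, 3 or 5 LEFS points, equal in both arms; retrieval of half or all of the missing scores; about 23 patients per feasibility arm.

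**1. The plan's own figure.** n per arm = 2 × (18.4 × 1.12)² × (1.960 + 0.842)² / 9² = 82.3, rounded up to 83. Then 83 / 0.65 = 127.7, so 128 per arm and 256 in total. The stated sample size reproduces and is not in dispute.

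**2. Candidates for telephone completion if the feasibility rates recur.** Intervention 128 × 0.09 = 11.5, about 12. Usual care 128 × 0.35 = 44.8, about 45.

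**3. Telephone share of the observed scores.** With missing rate q and retrieved fraction r, the share is p = qr / (1 − q + qr).

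- All retrieved: 9% v 35%, a gap of 26 percentage points.
- Half retrieved: 0.045 / 0.955 = 4.7% v 0.175 / 0.825 = 21.2%, a gap of 16.5 percentage points.

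**4. Bias in the arm difference.** Size = m × gap in share, treating the 12-month contrast as a difference in means.

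| Assumed shift | Half retrieved | All retrieved | All retrieved, as % of MCID |
|---|---|---|---|
| 2 points | 0.33 | 0.52 | 6% |
| 3 points | 0.50 | 0.78 | 9% |
| 5 points | 0.83 | 1.30 | 14% |

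If telephone scores run higher than postal ones, the bias favours usual care; if lower, the intervention. An interviewer effect that differs by arm would be additional and cannot be quantified from the documents.

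**5. Scale against sampling error.** With all scores retrieved, the unadjusted standard error is 18.4 × √(2/128) = 2.3. The largest bias is 1.30 / 2.3 = 0.57 standard errors, which would raise a nominal 5% error rate to about 9%. A bias of 0.78 gives about 6%.

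**6. Precision of the feasibility contrast.** Taking 2/23 v 8/23 as the counts behind "9 % in the intervention group and 35 % in the usual-care group", the gap is 26 percentage points with a 95% confidence interval of about 2 to 47 (Newcombe). Fisher's exact test gives p = 0.07. The direction is plausible and the size is poorly known.

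**The case against.** A reader might infer that staff who know the allocation will make the LEFS calls, and that mode will differ by arm at 12 months. The documents support neither as fact.

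- **The caller is not identified.** Telephone completion is mentioned as an example, and Assessment times says only that non-responders get a call. Knowledge of the arm is inferred from the general Randomisation sentence. Call procedures and mode fields would usually sit in the full protocol or working instructions, so their absence from an article is no finding. This stands. The point rests on the blanket statement and its reason, which are on the page.
- **The 9% and 35% are not 12-month postal non-response in this trial.** They are missing LEFS scores at 6 months in a small study and may include withdrawals or incomplete forms that a call would not recover. A postal reminder also comes before any call. This stands, so the uneven split is conditional. The planners did, however, rely on this study when they allowed for 35% missing data and added telephone completion.
- **The size depends on assumed shifts.** This stands. The 1.3-point maximum needs the full feasibility gap, complete retrieval and a 5-point shift together.
- **Lack of blinding is already acknowledged, and the respondent knows the arm anyway.** This is true for self-report. Masking the caller removes only a secondary component, but the Discussion does not cover that component, and it is the avoidable one.
- **A postal-only analysis would not settle the matter.** It would drop a selected group and bring back the differential missingness that the calls are meant to reduce. This stands, and such an analysis is not proposed here as a test of mode.

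**Conclusion.** The point holds in a limited, conditional form. The reason given for not blinding trial personnel does not extend to staff who complete the LEFS by telephone, and the acknowledged limitation covers only participants' own knowledge of their arm. If the feasibility pattern recurs, the primary outcome difference could carry a bias of about 0.3 to 0.8 points (half retrieved) or 0.5 to 1.3 points (all retrieved). Those ranges rest on assumed shifts of 2 to 5 points that are equal in both arms. Against "The minimal clinically important difference (MCID) for the LEFS is 9 scale points", this is small but systematic, and its direction is unknown. It does not show that the trial is biased or that telephone retrieval should be dropped; retrieval is worth keeping. It supports an inexpensive change to a stated rule.

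**What to change.** 1. In the Randomisation section, limit the statement to participants and treating physiotherapists, and say that staff who complete the LEFS by telephone are masked to allocation where feasible.
2. Have existing staff make these calls from a list without allocation, using a fixed script that puts the LEFS before any other question and asks participants not to reveal their arm. Where the rota allows, use someone who did not make the class-survey calls.
3. For each LEFS, record the mode (post or telephone) and any unmasking. Report mode by arm at each time point, above all at 12 months.
4. Treat any analysis by mode as supportive only, and do not read a postal-only result as isolating the mode effect.
5. Extend the blinding limitation in the Discussion to telephone completion.

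The cost is a call list without the arm column, a script, and fields for mode and unmasking. No extra staff, patients or visits are needed. The downsides are rota constraints in a small team and occasional unmasking by participants. The change helps only calls still to be made.
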